### Harms and Adverse Events

There are few reports of severe adverse events (SAEs) regarding transperineal prostate biopsies and local anaesthesia for biopsies. The main expected adverse events or side effects are listed at Table 2, and the participants will be informed of the risk for these adverse events or side effects before registration. The expected incidence of the adverse events is based on both our previous data and the literature (18). All complications and adverse events that occur from the date of registration to 1 week after the biopsy will be recorded by a research nurse. SAEs are defined as any of the following: (1) death; (2) life-threatening; (3) hospitalisation; and (4) disability or permanent damage. SAEs will be recorded immediately and then sent to the ethics committee and the APROPOS monitoring board within 24 h.

**Table 2 T2:** Other side effects that may occur in this trial besides pain.

**Side effect**	**Expected probability**	**Outcome**
Hematuria	2 in 3 men	Self-resolving, 3–14 days
Hematospermia	3 in 10 men	Self-resolving, 1–2 months
Bleeding in perineal	1 in 10 men	Self-resolving, 1–12 hours
Bleeding in rectum	1 in 50 men	Self-resolving, 1–3 days
Lower urinary tract symptoms	1 in 10 men	Self-resolving, 1–7 days
Transient erectile dysfunction	1 in 10 men	Self-resolving, 2–3 weeks
Urinary retention	1 in 30 men	Indwelling catheter, 3–7 days
Discomfort when passing urine	2 in 3 men	Self-resolving, 1–3 days
Discomfort in the rectum	2 in 3 men	Self-resolving, 1–3 days
Urinary tract infection	1 in 100 men	Oral antibiotics, 3–7 days
Fever	None	Intravenous antibiotics 3–7 days
Vasovagal event	1 in 50 men	Self-resolving, 0.5–2 h
Anaesthetic allergy	None	Antiallergy treatment, 0.5–3 h

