**Contact with patient**								
	**Visit 1**	**Visit 2**						**Visit 3**
	**0**	**Pre-biopsy**	**Biopsy procedure**	**1-min post-biopsy**	**1-h post-biopsy**	**6 h post-biopsy**	**24 h post-biopsy**	**2 weeks post-biopsy**
Consent	×							
Screening	×							
Baseline characteristic	×							
PSA	×							
MRI	×							
Randomisation	×							
Perineal nerve block (Perineal nerve block arm)		×						
Periprostatic block (Periprostatic block arm)		×						
Transperineal prostate biopsy (12-core systematic biopsy with/without cognitive targeted biopsy)			×					
Blood presure measurement		×	×	×				
Heart rate measurement		×	×	×				
Breath rate measurement		×	×	×				
External manifestations assessment			×					
NRS pain score assessment				×	×	×	×	
Anaesthesia satisfaction assessment							×	
Pathological assessment								×
Withdrawal	Complete as required at any time following registration							
SAE	Complete as required at any time following registration							

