▸ Post-biopsy pain severity score, for which pain will be evaluated by the NRS at 1, 6, and 24 h after the prostate biopsy.▸ Changes in blood pressure, heart rate and breathing rate during the biopsy procedure, which will be measured and recorded by a multi-parameter monitor from 1 min prior to anaesthesia (initial value) to 1 min after the prostate biopsy. The change will be defined as the difference between the average value during the anaesthesia and biopsy procedures and the initial value. Additionally, the difference between the maximum value and the initial value will be assessed.▸ External manifestations of pain during biopsy, which will be assessed by a research nurse who will be blinded to the block arm during the biopsy procedure. The pain assessment will be divided into five parts: the degree of facial expression (0 points for no particular expression or smile; 1 point for an occasional grimace or frown, a withdrawn expression, or a disinterested expression, 2 points for frequent or constant quivering chin or a clenched jaw), the degree of activity (0 points for lying quietly or being in a normal position, 1 point for slight contractions of the hip muscles or slight movements of hip, 2 points for severe contractions of the hip or lifting the hip out of the bed), the degree of voice expression (0 points for quiet or normal communication, 1 point for an occasional moan or weeping sound, 2 points for constant moaning or sobbing and screaming), the degree of pacification (0 points for being peaceful and not requiring pacification, 1 point for being able to be comforted easily, 2 points for being difficult to comfort) and the degree of cooperation (0 points for being calm and cooperative, 1 point for language resistance, 2 points for body resistance).▸ Anaesthesia satisfaction, or patient satisfaction with overall anaesthesia, which will be measured by a questionnaire at 24 h after the biopsy. Five items will be included to evaluate satisfaction: whether the pain during the biopsy was less severe than expected (scores from 0 to 10, where 0 represents far less severe, and 10 represents far more severe than expected); whether the pain after anaesthesia was less severe than the pain during anaesthesia (scores from 0 to 10, where 0 represents far less severe and 10 represent far more severe); weather the patient is satisfied with the overall feeling of the biopsy (scores from 0 to 10, where 0 represents the highest level of satisfaction, and 10 represents the lowest level of satisfaction); whether the patient would recommend this type of biopsy to other patients (scores from 0 to 10, where 0 represents they would highly recommend, and 10 represents they would definitely not recommend it); and whether the patient would still want to choose this way if they have to undergo another biopsy (scores 0 to 10, where 0 represents very willing to choose it and 10 represents extreme reluctance).▸ The detection rate for prostate cancer, defined as the proportion of men with prostate cancer among those who undergo a prostate biopsy.▸ The detection rate for clinically significant prostate cancer, defined as the proportion of men with prostate cancer of International Society of Urological Pathology (ISUP) grade 2 or higher, according to the 2014 ISUP classification, among men who undergo a prostate biopsy.▸ Adverse events, which will be recorded 7 days after this trial. These events mainly include haematuria, vagal reflex, infection, urinary retention and other adverse events identified by the Common Terminology Criteria for Adverse Events (CTCAE).

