## Trial Status

This RCT was first registered online at ClinicalTrials.gov on August 2, 2020. The trial is start recruiting on August 13, 2020. Recruitment is anticipated to continue until September 15, 2021, with the 1-month follow-up expected to be completed on October 15, 2021.

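### The non-serious adverse-event window closes 1 week after biopsy, matches no scheduled contact, and is shorter than three of the durations in the trial's own side-effect table

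*Protocol article*

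**What the plan says.** All references are to the protocol article.

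- **Harms and Adverse Events**, text: "adverse events that occur from the date of registration to 1 week after the biopsy will be recorded".
- **Outcomes**, last item of the secondary list: "Adverse events, which will be recorded 7 days after this trial".
- **Table 1**: the contacts after biopsy are at 1 min, 1 h, 6 h, 24 h and then Visit 3, "2 weeks post-biopsy". Only pathology is marked at Visit 3. Serious adverse events have their own row, "Complete as required at any time following registration". There is no row for non-serious events.
- **Table 2** (in Harms and Adverse Events):
  - hematospermia, 3 in 10 men, "Self-resolving, 1–2 months"
  - transient erectile dysfunction, 1 in 10, "Self-resolving, 2–3 weeks"
  - hematuria, 2 in 3, "Self-resolving, 3–14 days"
- **Trial Status**: recruitment to September 15, 2021, "with the 1-month follow-up expected to be completed on October 15, 2021".

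**The concern.** Adverse events are a listed secondary outcome, and the two arms place anaesthetic at different sites. The recording rule should therefore be clear enough for every centre to apply in the same way, and it should fit the contacts at which patients are seen. Here the window has two anchors and ends on a day with no scheduled contact. It also closes before some of the events the trial itself expects would have run their course. The trial might then be unable to say whether erectile dysfunction was in fact transient or hematospermia in fact self-resolving. It could also miss non-serious events that a man first notices in the second week.

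**Working it through.** **1. The anchor.** Harms and Adverse Events counts the week from the biopsy. Outcomes counts 7 days from the trial, with no per-patient date. If the trial is taken to end at biopsy, the two agree at day 7. If it is taken to end at Visit 3, the Outcomes wording gives 14 + 7 = 21 days. If it ends at the follow-up in Trial Status (September 15 to October 15 = 30 days), it gives 30 + 7 = 37 days. The Harms text makes day 7 the natural reading, but the Outcomes wording does not fix it.

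**2. The schedule.** Table 1 has no contact between 24 h and 2 weeks, so day 7 falls in a gap. The 2-week visit has no adverse-event item. The 1-month follow-up in Trial Status is not a column of Table 1.

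**3. Window against expected duration.** Of the 13 rows of Table 2, 10 have durations of 7 days or less. The other three are below, with expected cases = 190 × Table 2 probability.

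| Event | Expected cases in 190 | Stated duration | Against a 7-day window |
|---|---|---|---|
| Hematospermia | 190 × 0.3 = 57 | 1–2 months | whole range beyond |
| Transient erectile dysfunction | 190 × 0.1 = 19 | 2–3 weeks | whole range beyond |
| Hematuria | 190 × 2/3 = 126.7 | 3–14 days | upper part beyond |

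These are total expected cases, not missed cases. Table 2 gives time to resolution, whereas the Harms rule includes an event by when it occurs. Hematospermia that begins on day 2 is counted even if it lasts two months; only its resolution is unseen.

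**4. What could be missed.** Let f be the share of cases with onset or first recognition after day 7. The article gives no onset times, so f is an assumption. Missed cases = expected cases × f.

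| Assumed f | Hematospermia | Erectile dysfunction | Hematuria |
|---|---|---|---|
| 0 | 0 | 0 | 0 |
| 10% | 5.7 | 1.9 | 12.7 |
| 25% | 14.2 | 4.8 | 31.7 |
| 50% | 28.5 | 9.5 | 63.3 |

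**5. Effect on an arm comparison.** With the same f in both arms, each recorded risk is the true risk × (1 − f). The risk difference shrinks by (1 − f) and the risk ratio does not change. To illustrate with an assumed 30% against 15%: at f = 25% the recorded risks are 22.5% and 11.25%. The difference falls from 15 to 11.25 points and the ratio stays at 2. With no true arm difference there is nothing to shrink.

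**The case against.** The strongest case against is that duration is not onset. A reader might infer from Table 2 that the 57, 19 and 127 expected cases go unrecorded, or that the harm comparison is biased towards no difference. The article does not support either. Cases that start by day 7 are included however long they last. No onset times are given, and Table 2 states one probability per event for all men, so no arm difference is documented. Even with late onset, dilution needs a true difference, and it depends on the measure used. This objection stands in full.

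A reader might also infer that all harm recording stops at day 7. Table 1 contradicts that for serious events, so a late infection or retention leading to hospitalisation would still be reported. This also stands.

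Further, both texts say 7 days or 1 week and the Harms wording settles the anchor. The events named in Outcomes are mostly short-lived, with retention and urinary tract infection listed at 3–7 days. A condensed article may also leave follow-up procedures to the full protocol. These arguments reduce the weight of the point but do not remove it. The printed window, schedule and durations do not fit together, and the 1-month follow-up cannot be matched to Table 1.

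**Conclusion.** The point holds as a minor one. For non-serious events the stated window ends at 1 week, is loosely anchored in Outcomes, and coincides with no contact in Table 1. It is shorter than the expected duration of hematospermia and transient erectile dysfunction, and than the upper range for hematuria. What may be lost is late-occurring or late-recognised non-serious events, and the persistence or resolution of ongoing ones.

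The number of lost cases cannot be derived. It is zero if all onset is by day 7 and otherwise grows in proportion to an assumed late share. The firmer statement that arm differences in harm will be under-counted is not supported, because it needs both late onset and a true arm difference, and the article documents neither. The conclusion assumes that Table 1 lists all planned patient contacts. The primary pain outcome is unaffected.

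**What to change.** - Record non-serious adverse events from registration through the existing 2-week Visit 3. Ask there about each Table 2 event and whether it is ongoing.
- Add a non-serious adverse-event row to Table 1.
- State the same biopsy-anchored window in Outcomes and in Harms and Adverse Events.
- Reconcile the 1-month follow-up in Trial Status with Table 1.

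The cost is a few extra questions at a visit that already exists. There is a limit: by Table 2, hematospermia would usually still be ongoing at 2 weeks, so Visit 3 would record its status, not its resolution. A contact at 1 month would not cover the full 1–2 month range either, so adding one is not a necessary part of this fix.

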### Blinding

All participants and research nurses measuring or recording the results will be unaware of the intervention group (perineal nerve block or periprostatic block). The researcher who collects or enters the data will also be blinded to the allocation. The urologist who conducts the anaesthesia will be blinded to all other data, including the name and trial number of the participant, and will not aid in assessing the outcomes or processing the data. The other urologist who will perform the prostate biopsy will be unaware of the allocation, and the pathologist who will report the pathologic outcomes will be unaware of all patients' clinical information.

### Data Collection and Monitoring

After informed consent is obtained from the patients, the data will be collected by a research nurse who is blinded to the allocation to ensure the integrity of evaluation and prevent bias. Demographic information, including age, body mass index (BMI), PSA level, DRE results, prostate volume and American Society of Anesthesiologists (ASA) classification will be collected before anaesthesia. The pain score will be measured and recorded *via* form 1 (Figure 4) at 10 min, 1, 6, and 24 h after the biopsy. Additionally, the pain of phlebotomizing and the pain at the first moment the needle touches the skin during anaesthesia will be used as the reference and baseline for the pain assessment (form 1). During the biopsy, the external manifestations of pain will be measured *via* form 2 (Figure 5), and the blood pressure, heart rate and breathing rate will be recorded by a multi-parameter monitor. The site of needle core will be reported, because the targeted cores of the anterior zone might be associated with more pain in comparison with those of the peripheric zone (19). Before the participant is dismissed, the anaesthesia satisfaction assessment will be collected *via* form 3 (Figure 6). The pathologic data will be collected within 2 weeks after the biopsy. All of these data will be entered into a particular database. An independent monitor from the APROPOS operation group will check the quality of the data at least twice a week. The monitor may pose queries to the data, and the validity of the data will not be confirmed unless the questions have been resolved.

**Figure 4 F4:**
[figure not shown]
Form 1.

**Figure 5 F5:**
[figure not shown]
Form 2.

**Figure 6 F6:**
[figure not shown]
Form 3.

## Discussion

We initially developed the perineal nerve block based on an anatomical study and then conducted a pilot trial to verify its efficacy and safety preliminarily.

To confirm the findings and ensure the results more generalizable, we plan to conduct this multicentre randomised controlled trial, used rigorous randomised design and blinding method.

Apart from the subjective NRS pain scores reported by the patients, the external manifestations of pain during the biopsy, and the indicator changes displayed on the monitor will be considered to make the pain control assessment more comprehensive and multidimensional.

In conclusion, this trial will determine the efficacy of the perineal nerve block in controlling pain in patients undergoing prostate biopsy *via* the transperineal approach.

## Trial Status

This RCT was first registered online at ClinicalTrials.gov on August 2, 2020. The trial is start recruiting on August 13, 2020. Recruitment is anticipated to continue until September 15, 2021, with the 1-month follow-up expected to be completed on October 15, 2021.

## Ethics Statement

Ethical approval was obtained from the Ethics Committee of all centres (Supplementary Material). All participants will sign a consent form prior to randomisation. The results of this trial will be disseminated to an international peer-reviewed journal and presentations at international or national academic conferences.

## Patient and Public Involvement

The patients and public were not involved in the contribution of the design, recruitment or conduction of the trial. Each participant will be informed of the latest results at follow-up and received a summary of the main finding at the end of the trial.

